### Sample size

Sample size calculation for the primary study population is based on the primary endpoint. The literature available at the time of sample size planning showed that there was a rehospitalisation rate of 55% after alloHCT in a German population [10]. Given that deceased patients were typically hospitalised beforehand, it can be inferred that the 55% figure accurately represents the routine clinical care. The SPIZ program should reduce the mortality or disease-specific rehospitalisation rate to 35% or less. The case number calculation was performed with a one-sided Fisher test. Given a significance level of 5% and a yielded power of 80%, it is assumed that 143 patients in the intervention group and 143 patients in the control group are required (calculated with GPower 3.1). With an estimated drop-out rate of 5%, 302 patients must be included.

While disease- and cell therapy-specific rehospitalization or death includes all complications typically associated with the underlying hematological condition or cell therapy, other reasons for rehospitalization or death are defined as independent, e.g., joint replacement due to arthrosis, or an accident. The analysis of the primary endpoint will be conducted one year after primary hospital discharge of the last enrolled patient. Death or rehospitalization are considered equivalent primary endpoints.

Recruitment of health care providers involved in SPIZ (secondary study population) for twelve qualitative interviews starts 18 months after initiation of patient enrollment.

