## Introduction

Cellular therapies like allogeneic hematopoietic cell transplantation (alloHCT) and chimeric antigen receptor T (CAR T)-cell therapy have led to an improvement in prognosis of patients with hematologic diseases [1, 2]. AlloHCT has been established over the past decades as a standard treatment for various hematological diseases [2]. Since 2018, CAR T-cell therapy has been approved for patients with lymphoma and certain types of leukemia in Germany [3, 4]. Both alloHCT and CAR T-cell therapy require a high level of expertise, specific structural requirements such as the accreditation of treatment centers, and substantial personnel resources for the primary hospital stay and post-treatment care [5, 6]. In Germany, regulatory and administrative requirements are governed by a decision of the Federal Joint Committee (Gemeinsamer Bundesausschuss, G-BA) [7].

The continuous increase in the number of patients treated with innovative cellular therapies has led to a growing population requiring post-treatment care [2]. After discharge from the primary hospital stay for cellular therapy, patients undergoing these innovative treatments remain at high risk of mortality and severe complications, including life-threatening infections, organ toxicities, and disease relapse following cellular therapy in general, as well as graft-versus-host disease (GvHD) after alloHCT and cytokine release syndrome (CRS), or neurotoxicity, such as immune effector cell-associated neurotoxicity syndrome (ICANS), after CAR T-cell therapy, in particular. In a large Japanese trial among alloHCT recipients, 2-year non-relapse mortality (NRM) was reported to be 16% [8]. Within a large US-American cohort, 31% of patients required readmission within the first 100 days after alloHCT [9]. Within a German cohort rehospitalizations after alloHCT were as high as 55% [10]. NRM in CAR T-cell therapy was reported to be disease-specific, e.g., reaching 10.6% in mantle cell lymphoma patients [11]. 41% of CAR T-cell therapy patients needed rehospitalization within an US-American cohort with 9% intensive care unit readmissions [12].

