### Eligibility criteria

The target population comprises all adult patients (≥ 18 years) after alloHCT or CAR T-cell therapy.

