### Enrollment, randomization and patient pathway

After enrollment, which takes place not later than eight days following discharge from the primary inpatient stay for cellular therapy, patients are randomly assigned in a 1:1 ratio to either the SPIZ program or the control group. The randomization is stratified according to patient age (< 60 years or ≥ 60 years) for each of the three cellular therapy centers individually using the REDCap (Research Electronic Data Capture)-based project database. Prior to the commencement of the study, age-group-specific randomization lists have been created through block randomization, employing permuted blocks of variable length. These randomization lists are prepared by the Dresden Coordination Center for Clinical Trials, which is also responsible for the preparation and administration of the REDCap project database. The randomization result is displayed to study staff in REDCap once informed consent and eligibility based on the inclusion and exclusion criteria have been documented. Depending on group allocation, patients proceed through either the SPIZ pathway or standard routine care (Fig. 2). Patients are scheduled to receive treatment for a minimum duration of 12 months and a maximum duration of 24 months.

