### Hypotheses and outcomes

The primary hypothesis is that patients receiving the SPIZ intervention following cellular therapy (intervention group) experience better health outcomes in terms of lower mortality and fewer hospital readmissions than patients receiving routine clinical care (control group). The target population comprises all adult patients with hematologic diseases who undergo alloHCT or CAR T-cell therapy at one of the three participating centers.

Efficacy will be evaluated using a composite primary endpoint comprising mortality and disease-related rehospitalization. The latter is defined as unplanned rehospitalization due to complications typically associated with either the underlying hematologic disease (e.g., disease progression) or cellular therapy. Such complications include infections and organ toxicities following either therapy, GvHD following alloHCT, and CRS or neurotoxicity, such ICANS, following CAR T-cell therapy. The primary endpoint will be evaluated by confirmatory statistical analysis 12 months after cellular therapy.

Secondary hypotheses with corresponding outcomes and data sources are listed and described in Table 1.

**Table 1 Tab1:** Overview of the secondary hypotheses. The four secondary hypotheses to be examined are listed along with their corresponding secondary outcomes and the respective data sources or scales

Secondary hypotheses	Secondary outcomes	Data source / scale
a) SPIZ leads to improved longitudinal clinical outcomes	◼ Mortality ◼ Complications, e.g., infections, GvHD (alloHCT), CRS (CAR T-cell therapy), neurotoxicity (CAR T-cell therapy), relapse, and death assessed by incidence and duration (as feasible) ◼ Rates and duration of unplanned rehospitalizations ◼ Symptom burden, including nutrition, body weight, body temperature, skin changes, bowel habits, and neurological symptoms ◼ Laboratory values ◼ Therapy adjustments ◼ Conducted assessments, e.g. staging, pulmonary function testing, echocardiography	REDCap-based project database, SMILe system
b) SPIZ leads to improvements in QoL and patient empowerment	QoL assessed using established questionnaires	EORTC QLG Core Questionnaire QLQ-C30 and module for low-grade non-Hodgkin lymphoma QLQ-NHL-LG20 [17], NCCN Distress-Thermometer (German version) [18]

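### The 55% planning rate is an alloHCT figure not shown to fit the mixed alloHCT/CAR T population or the cause-restricted endpoint, and therapy type is adjusted for only after the fact, if at all (minor)

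*Protocol article*

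**What the plan says.** All points are in the protocol article.

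- **Population.** Eligibility criteria: "The target population comprises all adult patients (≥ 18 years) after alloHCT or CAR T-cell therapy". Hypotheses and outcomes repeats the pooled definition: "adult patients with hematologic diseases who undergo alloHCT or CAR T-cell therapy at one of the three participating centers".
- **Planning rate.** Sample size reports that "there was a rehospitalisation rate of 55% after alloHCT in a German population" and then argues, on the ground that patients who died had usually been admitted first, that "it can be inferred that the 55% figure accurately represents the routine clinical care". The target under SPIZ is 35% or less. A one-sided Fisher test at 5% with 80% power is said to need 143 per group, or 302 in total with 5% dropout.
- **CAR T figure.** The Introduction gives a figure for the other therapy: "41% of CAR T-cell therapy patients needed rehospitalization within an US-American cohort". No time window is stated.
- **Endpoint.** Hypotheses and outcomes counts death and "unplanned rehospitalization due to complications typically associated with either the underlying hematologic disease" or the cellular therapy, evaluated at 12 months.
- **Randomization.** Enrollment, randomization and patient pathway stratifies by age group (below 60, or 60 and over) within each of the three centers. Therapy type is not a stratum.
- **Analysis.** The section on the primary hypothesis and secondary hypothesis a) specifies Fisher's exact test on the two arms, with logistic or Poisson regression for effect sizes. Adjustment, subgroup or sensitivity analyses follow only if serious bias appears despite randomization. Therapy type is not named.
- **Enrollment.** Results reports 153 patients per group; recruitment is closed.

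**The concern.** The planning sentence has to carry a rate across two gaps, and its one argument crosses neither. That deceased patients were usually admitted first may justify using a rehospitalization rate for a composite of rehospitalization and death. It does not take an alloHCT rate to a population that includes CAR T patients. Nor does it take a rate quoted without cause, planned status or time window to a 12-month endpoint limited to unplanned admissions for named causes.

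Two things follow. If the control rate in the enrolled mix is below 55% while SPIZ achieves exactly 35%, the contrast is smaller than planned. And therapy type, which the endpoint definition itself treats as relevant (GvHD after alloHCT, CRS or neurotoxicity after CAR T), enters the effect estimate only through a judgment made once group differences are visible. An adjustment chosen that way is open to the question whether the result influenced it.

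**Working it through.** **1. The plan's own figure.** Inputs from Sample size: 55% versus 35%, one-sided Fisher, alpha 0.05. Exact power is the sum of Bin(x; n, p1) × Bin(y; n, p2) over all tables (x, y) with one-sided Fisher p ≤ 0.05.

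- n = 85 per arm is the smallest that reaches 80% (80.7%).
- n = 143 gives 95.6%, and n = 153 gives 96.1%.
- The dropout step is right: 286 / 0.95 = 301.05, rounded up to 302.

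So 143 per arm does not follow from the stated rates at 80% power. It would roughly fit 55% versus 40% (79.8% at 143). The surplus matters here because it absorbs much of the effect of a lower control rate.

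**2. Mixed control rate.** The article gives no CAR T share, so the share s is an assumption, taken from 20% to 50%. The article's 41% is used for CAR T as an illustration only.

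Control rate c = 0.55 × (1 − s) + 0.41 × s. For s = 0.30: 0.385 + 0.123 = 0.508.

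**3. One-sided Fisher power under three readings of the planned effect:** intervention rate fixed at 35%; same relative reduction (35/55 = 0.636); same 20-point difference.

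| CAR T share | Control rate | 35% fixed, n = 143 | 35% fixed, n = 153 | Relative, n = 153 | 20 points, n = 153 |
|---|---|---|---|---|---|
| 0% | 55.0% | 95.6% | 96.1% | 96.1% | 96.1% |
| 20% | 52.2% | 88.9% | 89.8% | 94.5% | 96.3% |
| 30% | 50.8% | 83.6% | 84.7% | 93.6% | 96.5% |
| 40% | 49.4% | 77.0% | 78.1% | 92.6% | 96.8% |
| 50% | 48.0% | 69.0% | 70.3% | 91.6% | 97.0% |

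At a 35% share with the intervention rate fixed at 35%, power is 80.5% (n = 143) and 81.6% (n = 153). The 80% line is therefore crossed between shares of 35% and 40%, and only under that reading.

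**4. Chance imbalance in therapy type.** At an assumed 30% share and 153 per arm, the 95% range for the difference in share between arms is 1.96 × √(2 × 0.3 × 0.7 / 153) = 10.3 points. Multiplied by the 14-point gap between 55% and 41%, this shifts the crude event difference by up to about 1.4 points.

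**5. Precision within CAR T.** At a 30% share there are about 46 per arm (0.3 × 153). With assumed rates of 41% and 30%, the 95% half-width of the risk difference is 1.96 × √((0.41 × 0.59 + 0.30 × 0.70) / 46) = 19.4 points.

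**The case against.** The strongest reply is that little depends on the sentence. Recruitment is closed, so neither the strata nor the sample size can change. The target is 35% or less, not exactly 35%, and power is high if the planned reduction holds in relative or absolute terms. A chance imbalance worth 1.4 points is small beside a planned 20-point effect, and the test's error rate already allows for it. Leaving one prognostic factor out of the strata is a choice, not an error. Covariates and subgroups are commonly left to an analysis plan, which exists but is not shown. Most of this stands and is why the point is minor. What does not fall away is that the article itself states an imbalance-triggered adjustment rule, and itself asserts that 55% is accurate.

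Three stronger readings are tempting and not supported:

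- *That the pooled conclusion does not describe the enrolled population.* The target population is defined as both therapies together. A randomized comparison of the pooled arms is valid for that mix and addresses its average effect. Whether the effect is equal in each therapy is a separate question.
- *That the 55% counts any rehospitalization.* The article leaves the figure unqualified. It does not say that all causes are included, only fails to show that the endpoint's causes are.
- *That the mixed control rate must be below 55%.* The 41% is a US rehospitalization figure without a time window and is not stated to include deaths. The 12-month composite after CAR T could be higher or lower.

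**Conclusion.** The claim that 55% accurately represents routine care is unsupported for this trial: the figure is for alloHCT only and is not shown to match either the mixed population or the cause-restricted composite. Stated power is missed only if two conditions hold together: a CAR T share approaching 40% and an intervention rate of exactly 35%. This rests on an assumed share and on 41% as the CAR T composite rate, neither of which the article establishes. Otherwise power at 153 per arm is above 80%, and at least 91% under the relative or absolute reading for shares up to 50%. These powers assume all 153 per arm contribute to the analysis.

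The confirmatory test is sound for the pooled population. The contingent adjustment rule is weaker than a fixed one and is easily replaced. Severity: minor.

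**What to change.** 1. **Planning sentence.** Say that 55% is a rehospitalization figure after alloHCT, not shown to match the cause-restricted composite or the alloHCT/CAR T mix. Restate power at 153 per arm over a range of control rates, and reconcile 143 per arm and 80% power with the stated 55% and 35%.
2. **Adjustment.** Before data lock, replace the imbalance-triggered rule for therapy type with a prespecified adjustment for therapy type, age group and center in the regression effect estimate. Keep Fisher's exact test as the confirmatory test.
3. **Supportive reporting.** Give the 12-month risk difference with its interval by therapy type, and make no therapy-specific claim beyond what that interval supports.

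Cost: a few sentences and one additional analysis on a variable known at baseline; nothing changes for patients or sites. The gain in precision from adjustment will be small, and the CAR T interval will be wide (about ±19 points in the example above). The benefit is mainly that the adjustment is settled before results are seen.

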### Data analysis regarding primary hypothesis and secondary hypothesis a)

The confirmatory test of the primary outcome at 12 months will be performed using Fisher’s exact test. All outcomes of secondary hypothesis a) are presented descriptively for the intervention and control groups according to the respective survey dates. The same applies to the primary combined outcome at time points 6, 18, and 24 months. Metric values will be compared between groups in terms of their means or, in the case of skewed distributions, their medians; categorical values will be compared in terms of their distributions. For events (death/ complication/ hospitalisation), survival time analyses and hazard ratios will be calculated. Logistic or Poisson regressions will be used to estimate effect size measures (odds ratios or relative risks). In addition, the control and intervention groups will be compared with regard to potential confounders. Should serious biases occur despite randomization, these will be addressed as appropriate through adjustments, subgroup analyses, or sensitivity analyses.

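### The sample size of 143 per arm does not follow from the stated 55% versus 35%, one-sided 5% and 80% power; those inputs need 85 per arm, so at least one of the stated figures is wrong

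*Protocol article*

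**What the plan says.** All inputs stand in one paragraph of the protocol article, under Sample size.

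- Control rate: the literature showed that "there was a rehospitalisation rate of 55% after alloHCT in a German population", and the article reasons that "it can be inferred that the 55% figure accurately represents the routine clinical care".
- Target rate: "The SPIZ program should reduce the mortality or disease-specific rehospitalisation rate to 35% or less".
- Test: "The case number calculation was performed with a one-sided Fisher test".
- Level and power: "Given a significance level of 5% and a yielded power of 80" per cent.
- Result: "it is assumed that 143 patients in the intervention group and 143 patients in the control group are required (calculated with GPower 3.1"). With 5% drop-out this becomes 302 in total.

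Allocation is 1:1 (Enrollment, randomization and patient pathway). The section on data analysis for the primary hypothesis names the same test: "The confirmatory test of the primary outcome at 12 months will be performed using" Fisher's exact test. The Results section reports that enrolment closed in January 2026 with 153 patients in each group. No other section gives a different effect size, power or level.

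**The concern.** A difference of 20 percentage points around 50% is large, and 143 per arm looks too many for it at a one-sided 5% level and 80% power. The paragraph gives every input that the calculation needs, so the figure can be checked without the full protocol or the SAP.

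This is the article's only justification for the size of the confirmatory comparison. As written, a reader cannot tell whether the trial was planned to detect 15 or 20 points, or whether it had 80% or about 96% power for the stated effect. That changes how a non-significant result would be read: it would be strong evidence against a 20-point effect but much weaker evidence against a 15-point one. The Discussion links a positive evaluation to long-term reimbursement, so the planned effect will be looked at closely.

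**Working it through.** **Inputs (Sample size section; allocation from the randomization section).** p1 = 0.55, p2 = 0.35, Fisher's exact test, one-sided, α = 0.05, power 0.80, 1:1 allocation. Stated n = 143 per arm.

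**Drop-out step.** 2 × 143 = 286, and 286 / 0.95 = 301.05, rounded up to 302. This reproduces, so the discrepancy lies before the drop-out allowance.

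**Rough check by normal approximation.** With p̄ = 0.45,

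n = [z₀.₉₅ √(2p̄(1−p̄)) + z₀.₈₀ √(p1(1−p1) + p2(1−p2))]² / (p1−p2)²

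= [1.645 × √0.495 + 0.842 × √0.475]² / 0.04 = (1.157 + 0.580)² / 0.04 ≈ 75.5, so 76 per arm.

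With continuity correction, n′ = (n/4)[1 + √(1 + 4/(n × 0.20))]² = (75.46/4)(1 + √1.265)² ≈ 85.2, so 86 per arm.

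**Exact calculation for the named test.** For each pair of event counts (x1, x2), the one-sided Fisher p-value is the lower hypergeometric tail given the total x1 + x2. Power is the sum of Bin(x1; n, p1) × Bin(x2; n, p2) over all pairs with p ≤ 0.05. For 55% versus 35%:

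| n per arm | Power |
|---|---|
| 84 | 79.97% |
| 85 | 80.7% |
| 143 (stated) | 95.6% |
| 153 (enrolled) | 96.1% |

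The stated inputs need 85 per arm, and 143 / 85 = 1.68.

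**Could another convention explain 143?** For 55% versus 35% at 80% power, a two-sided 5% level gives 96 (normal approximation), 106 (continuity-corrected) or 102 (Fisher). A one-sided 2.5% level gives 96 or 106 by approximation. None is near 143. A two-sided 1% level with the normal approximation gives 144, but this contradicts both the stated level and the stated test. A rate below 35% would need fewer patients, so the words allowing for a lower rate do not help.

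**Which inputs do give about 143?** One-sided 5% Fisher test throughout:

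| Rates | Smallest n for 80% | Power at 143 | Power at 153 |
|---|---|---|---|
| 50% vs 35% | 143 (142 gives 79.6%) | 80.01% | 81.1% |
| 55% vs 40% | 144 | 79.8% | 80.6% |
| 55% vs 35% | 85 | 95.6% | 96.1% |

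For 55% versus 35% at 95% power, the Fisher calculation gives 140 and the continuity-corrected approximation 142.

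**The case against.** The strongest reply is that the consequences are limited. Recruitment is complete, and the slip changes neither the endpoint, nor the test, nor the analysis population. At the 153 per arm enrolled, power at the declared level is at least 80% under each of the three readings above. All of that stands: this is an error of reporting, and the trial is not shown to be too small. It does not remove the contradiction, because the paragraph still asserts a combination of rates, power and n that cannot all be true.

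A reader might go further in four ways that the article does not support.

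- *The true target was 40%.* 55% versus 40% comes close, but 143 gives 79.8% and 144 are needed, whereas 50% versus 35% gives 143 exactly. The control rate may be the misstated figure, with 35% and 80% both as planned.
- *There is spare power, so the test should move to two-sided 5%.* Power at 143 would be 91.1% only if both 55% and 35% are right; under either 15-point reading it would be about 68 to 69%. A one-sided 5% level was openly declared, and changing it is a design decision, not an arithmetic correction.
- *Sidedness and level are missing from the analysis section.* They are stated under Sample size, the primary hypothesis is directional, and the analysis section names the same test. Repeating them can be left to the full protocol and SAP.
- *The registry entry repeats the error.* The article gives only a registration number, so what the registry says on this point is unknown.

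**Conclusion.** The Sample size paragraph contradicts itself. Its own inputs need 85 per arm, not 143, and 143 per arm gives 95.6% power, not 80%. At least one of the 55%, the 35% and the 80% is misstated. The candidates are a 15-point difference at 80% power (exact for 50% versus 35%, near for 55% versus 40%) and the stated 20-point difference at about 95 to 96% power. The article does not allow a choice between them.

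This conclusion assumes equal arms, as the article states, and exact unconditional power of Fisher's test. The normal approximations for the same inputs (76 and 86) lead to the same conclusion, so it does not depend on the method of calculation.

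**What to change.** Recover the inputs of the original GPower calculation and, before outcomes are analysed, correct the Sample size paragraph so that control rate, target rate, power and n agree.

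- If 55% and 35% are confirmed, restate the power as about 96% at 143 per arm.
- Otherwise, restate the rate or rates actually used.

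Neither correction should be published without that check, because choosing one by inference could replace one wrong figure with another. The cost is a search of the planning files and a short text correction; no further patients are needed, and the test and the declared one-sided 5% level stay as they are. Timing matters: first results are expected in mid-2027, and a planned effect corrected after the outcomes are known would look as if the data had driven it.
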